## Methods

### Description of Participants

Participants aged between 18 and 75 years will be recruited through posters and flyers at strategic points and by word of mouth in order to support diversity. More specifically, we will recruit from the University of New Mexico’s hospital, clinics, and facilities (both from the Main and North campuses), and from the Albuquerque area in New Mexico. After showing interest, potential participants will be thoroughly informed about the study’s risks and benefits, and they will be asked to answer a medical and physical activity history questionnaire in order to assess eligibility [35]. The inclusion criteria will be presence of prediabetes (fasting glycemia between 100 and 125 mg/dL or glycated hemoglobin [HbA_1c_] between 5.7% and 6.4%) or T2D (fasting glycemia 126 mg/dL or above or HbA_1c_ 6.5% or above), diagnosed by a medical doctor. Glycemic status will be confirmed by assessing a fasting blood sample. Exclusion criteria will be renal failure; liver disease; uncontrolled hypertension (>160 mmHg systolic and/or >100 mmHg diastolic); history of severe cardiovascular problems; inability to perform resistance exercise; being pregnant or trying to become pregnant during the course of the study; use of oral contraceptives; and in case of being treated with biguanides (metformin), being on them for less than 3 months. If eligible, before initiating participation, subjects will sign the informed consent form previously approved by the Institutional Review Board (IRB). Participants will be reimbursed for expenses incurred due to the research and resulting from it. Participation will be discontinued in case of withdrawal of consent or in case of injury or sickness (eg, skeletomuscular injury and having a cold). We will report reasons for withdrawal and discuss the reasons qualitatively. Adverse events related or nonrelated to the research protocol experienced by participants during the study will be carefully recorded and reported in the final manuscript.

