### CGM Assessment

Glycemic control will be assessed by a CGM device (Dexcom G6 Pro; Dexcom) every 5 minutes, over the ~48-hour experimental sessions. Reporting of variables will follow the most recent international guidelines consensus for clinical trials [48] and will include (1) time in range: 70-180 mg/dL; (2) time in tight range: 70-140 mg/dL; (3) time below range: <70 mg/dL; (4) time in level 1 hypoglycemia: 54-69 mg/dL; (5) time in level 2 hypoglycemia: <54 mg/dL; (6) time above range: >180 mg/dL; (7) time in level 1 hyperglycemia: 181-250 mg/dL; and (8) time in level 2 hyperglycemia: >250 mg/dL. Data will be reported as a percentage of time per day and as estimated hours and minutes per day. We will also report (9) average glucose concentration and (10) area under the curve, (11) glucose management indicator (used to predict long-term glucose exposure); (12) glycemia risk index (summary of the quality of glycemia), (13) glucose coefficient of variation; and (14) mean SD glucose (both are measures of dynamic glucose variability). Variables will be reported for the entire 48-hour collection period, for the first and second 24-hour periods, and stratified over 4 different periods: morning (6 AM to 12 PM), afternoon (12 PM to 6 PM), evening (6 PM to 12 AM), and nocturnal (12 AM to 6 AM) [11]. Individual data will be analyzed only if the percentage of data obtained is >70% of the anticipated amount of data collected during the collection period [48].

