### Statistical Analysis

The sample size was calculated using data from relevant literature using similar individuals and glucose-assessing tools (CGM) [11,14,52,53]. Conservative parameters were inserted in the G*Power program (Heinrich-Heine-Universität Düsseldorf, version 3.1.9.6) for a repeated measure ANOVA within interaction: effect size of 0.2 (for 24-hour average glucose concentrations), probability of error type **α** of 0.05, power (probability of error type 1 β) of 0.95, correlation among repeated measurements of 0.7 [54], and nonsphericity correction of 0.5 [55,56]. With these parameters, 15 individuals are required (actual power of 0.96). Considering a typical dropout rate of 25% to 40%, we will initially recruit 25 participants.

A collaborator outside the research team will double-enter data coded for allocation into a computer in separate spreadsheets, allowing the researcher responsible for data analysis to assess the data without access to allocation information. Allocation will only be revealed after statistical analyses are run. In case of doubts about data entry (missing values or values outside the reference range), the researcher responsible for data analysis will contact the collaborator outside the research team responsible for double entry of the data to check accuracy. There will be no interim analysis.

To ensure confidentiality, all study-related information will be securely stored at the study site. All participant information will be kept in locked file cabinets in areas with access controlled by the principal investigator. All laboratory specimens, reports, data collection, process, and administrative forms will be identified by a coded ID number only to maintain participant confidentiality. Records containing names or other personal identifiers, such as locator forms and informed consent forms, will be stored separately from study records identified by code number. No personal information from participants will be released outside the study. Full access to the complete dataset will be restricted to members of the research team.

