The statistical analysis will follow the principles of intention-to-treat analysis [57]. Thus, data from participants will be assessed as randomized, regardless of whether they received the randomized treatment, meaning that even if they fail to follow the physical activity and diet instructions, or fail to complete the sessions as required, their data will be included in the analyses. Furthermore, we will also analyze the data “per protocol” [58], meaning that participants who deviate from instructions will be excluded from the final analyses. Differences in results stemming from intention-to-treat and per-protocol analyses will be discussed accordingly. The available variables will also be compared between participants who withdraw from the study and those who complete the study.

The effect of resistance exercise on glycemic control will be calculated as the absolute and percentage change between control and resistance exercise situations. Data will be expressed as mean and SD, with a 95% CI. For the analysis of data normality, we will perform the Shapiro-Wilk test. For normally distributed data, ANOVA will be used with 1 source of variation (experimental condition). If a significant main effect is observed, the post hoc Tukey test will be conducted. For nonnormal data, the Kruskal-Wallis test or Friedman test will be used as appropriate. The effect size will be calculated and interpreted as follows: <0.2=no effect, 0.2-0.49=low effect, 0.5-0.79=medium effect, and >0.8=large effect [59,60]. The significance level is set at 5%. The Prism program (version 10.1.1, GraphPad Software) will be used to generate graphs and analyze results. This trial will be reported following the CONSORT (Consolidated Standards of Reporting Trials) guidelines [61-63].

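### None of the tests named for the intention-to-treat analysis makes a valid within-person comparison that also keeps a randomised participant with a missing session

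*Protocol article*

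**What the plan says.** All places are in the Methods of the protocol article.

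- **Principle (Statistical Analysis).** "The statistical analysis will follow the principles of intention-to-treat analysis". Participants are assessed as randomised. If they do not follow the diet or activity instructions, or "fail to complete the sessions as required, their data will be included in the analyses". A per-protocol analysis is added, which removes participants who deviate.
- **Tests (Statistical Analysis).** "For normally distributed data, ANOVA will be used with 1 source of variation (experimental condition"); for nonnormal data, "the Kruskal-Wallis test or Friedman test will be used as appropriate". No participant or period term is mentioned.
- **Sample size (Statistical Analysis).** The calculation is for a "repeated measure ANOVA within interaction" and gives 15. Then: "Considering a typical dropout rate of 25% to 40%, we will initially recruit 25 participants".
- **How sessions can be lost.** Description of Participants: "Participation will be discontinued in case of withdrawal of consent or in case of injury or sickness", with a cold as one example. CGM Assessment: "Individual data will be analyzed only if the percentage of data obtained is >70" percent of what was anticipated for the collection period.
- **Timing (Randomization and Blinding).** The order of sessions is allocated only after the fifth familiarisation session.

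**The concern.** Each participant is meant to complete High, Low and Control, so the comparison of interest is within person. A randomised participant may miss a whole session, or return too little CGM data in one. The named tests then offer two options. The paired ones discard that person's valid sessions and become a completers analysis under an intention-to-treat label. The unpaired ones keep the sessions but treat them as coming from different people, which gives up the crossover.

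Precision is at stake in a trial that may finish with 15 people, and so is the meaning of the label. There is also a possible bias. The Introduction expects high effort to bring discomfort, soreness and negative psychological responses. If those who respond worst leave after High, a completers analysis would understate the High-Low psychological difference, which is half of the hypothesis.

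The per-protocol rule has a related weakness: it removes the whole participant when only one session may have deviated.

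**Working it through.** **1. Plan's recruitment figure.** Required 15, dropout 25% to 40%: 15/(1 − 0.40) = 25 and 15/(1 − 0.25) = 20. The stated 25 reproduces at the 40% end, so the plan allows for as few as 15 completers.

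**2. How many randomised participants could be affected by dropout.** At 40%, 25 − 15 = 10 leave; at 25%, 25 × 0.25 = 6.25. All, some or none may leave after randomisation, so the range is 0 to 10. Failures of the 70% CGM rule would add to this for the glycaemic outcomes; the article gives no rate for them.

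**3. What each named test does with a participant who has one or two usable sessions.**

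| Test | Keeps the participant? | Respects the pairing? |
|---|---|---|
| Classical repeated-measures ANOVA | No | Yes |
| Friedman | No | Yes |
| One-way ANOVA on condition | Yes | No |
| Kruskal-Wallis | Yes | No |

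**4. Cost of ignoring the pairing.** With correlation ρ = 0.7 (the plan's value) and 15 completers, the variance of High − Low in SD² units is 2(1 − 0.7)/15 = 0.040. A one-way ANOVA judges the difference against 2/15 = 0.133, which is 1/(1 − 0.7) = 3.3 times too large.

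In power terms, take f = 0.2, ρ = 0.7 and three conditions, and assume sphericity. The paired F test on 15 completers has noncentrality 15 × 3 × 0.2²/(1 − 0.7) = 6 on 2 and 28 degrees of freedom, hence power 0.54; with 19 completers it is 0.66. One-way ANOVA on all data had simulated power of about 0.12 and 0.13 in the same two settings, with the leavers split evenly between departure after session 1 and after session 2. These figures compare the tests; they do not re-check the plan's N of 15.

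**5. Gain from using every available session.** Assume equal variances, ρ = 0.7, the variance components known, and the missing condition spread evenly. The information each participant carries on a difference between conditions (in 1/SD²) is:

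- three sessions: 1/(1 − ρ) = 3.333
- two sessions: (2 + ρ)/[3(1 − ρ²)] = 2.7/1.53 = 1.765
- one session: 1/3 = 0.333

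The variance of High − Low is 2 divided by the sum.

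| Randomised participants | Sum | Variance | Reduction |
|---|---|---|---|
| 15 completers only (all dropout before randomisation) | 50.00 | 0.0400 | 0% |
| + 10 with one session each | 53.33 | 0.0375 | 6% |
| + 3 with two, 3 with one | 56.29 | 0.0355 | 11% |
| + 5 with two, 5 with one | 60.49 | 0.0331 | 17% |
| + 6 with two sessions each | 60.59 | 0.0330 | 17% |
| + 10 with two sessions each | 67.65 | 0.0296 | 26% |

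The gain depends on when people leave as much as on how many do.

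**The case against.** Four points can fairly be made for the plan.

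- **The intention-to-treat sentence is mainly about non-adherence.** A session that was started but not done as prescribed can still yield CGM and scale data, and these can be analysed as randomised. This stands. A reader might infer that the intention-to-treat promise cannot be kept at all; the text does not support that. The difficulty is confined to sessions that never took place or that fail the CGM rule.
- **Not every named test drops people.** This is also right: one-way ANOVA and Kruskal-Wallis drop nobody. They keep everyone only by ignoring the pairing, so they do not rescue the plan.
- **The 25% to 40% applies to recruits.** Five familiarisation sessions and the strength tests precede randomisation, and those who leave in that phase are outside any intention-to-treat set. It would be wrong to infer that 25% to 40% of randomised participants will be lost. That is the upper bound; the lower bound for dropout is none.
- **Missing data are commonly left to an analysis plan.** True in general, but this article itself fixes the tests, and the mismatch lies between two things it states.

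On bias, the Introduction links high effort to lower long-term adherence. Nothing says that people will leave a three-session trial after High, and colds or injuries may have nothing to do with condition. The article also provides for payment to aid retention, reporting of withdrawal reasons, comparison of withdrawers with completers, and board review of dropout. These would help to describe selective loss, though they do not bring discarded sessions back into the analysis.

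The 70% rule might be read as removing the whole participant. It refers to the collection period, which the preceding sentence gives as 48 hours, so it most naturally acts on each session already.

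**Conclusion.** The concern holds in a limited form. For a randomised participant who misses a whole session or has an unusable CGM session, no named test gives a within-person comparison that retains the remaining data. Under the paired tests that suit the design, the intention-to-treat analysis then becomes a completers analysis.

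The size is uncertain and should be stated as a range. Dropout affects 0 to 10 of 25 participants. The variance of High − Low that could be saved runs from 0% to 26%, with 6% to 17% if all or half of 10 post-randomisation leavers go after a single session. These figures assume 15 completers, ρ = 0.7, equal variances and the missing condition spread evenly; the 0% end also assumes no CGM failures. Understatement of the psychological contrast is a plausible risk that the article neither demonstrates nor excludes.

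**What to change.** Replace the ANOVA, Kruskal-Wallis and Friedman tests as the intention-to-treat analysis with a linear mixed model: fixed effects for condition and period, a random participant effect, fitted by REML to every available session of every randomised participant. It is valid if sessions are missing at random. That covers, for example, departure after High that depends on the High response already recorded; it does not cover departure that depends on unobserved values.

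State that the 70% CGM rule acts on the session, as it most naturally reads. Apply the per-protocol exclusion to the deviating session rather than to the whole participant.

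The cost is a change of wording and possibly of software, made before allocation is revealed to the analyst, plus reliance on the missing-at-random and model assumptions. No change to sample size or conduct is needed for this point.

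### The mean, SD and 95% CI format is fixed for all data, including variables sent to a rank test; for time variables bounded at zero, if they prove sparse, such intervals can fall below zero and under-cover

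*Protocol article*

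**What the plan says.** In the protocol article, Statistical Analysis, the summary rule is a single sentence without exceptions: "Data will be expressed as mean and SD, with a 95% CI". The method for the interval is not named. The text then separates variables by distribution: "For the analysis of data normality, we will perform the Shapiro-Wilk test". Those that pass go to ANOVA. For the others, "For nonnormal data, the Kruskal-Wallis test or Friedman test will be used as appropriate". No median, IQR or other summary is attached to that second route. Just before the summary rule, the treatment effect is defined as a contrast: "The effect of resistance exercise on glycemic control will be calculated as the absolute and percentage change between control and resistance exercise situations".

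The section CGM Assessment lists the glucose outcomes. They include time below range and its two levels, among them "time in level 2 hypoglycemia: <54 mg/dL", and also "time in level 2 hyperglycemia: >250 mg/dL". On their scale it says: "Data will be reported as a percentage of time per day and as estimated hours and minutes per day". These outcomes are to be given for the whole 48 hours, for each 24-hour half and for four 6-hour parts of the day.

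**The concern.** The plan foresees nonnormal variables and changes the test for them, but leaves the estimate and interval unchanged. For such a variable the P value would come from ranks, while the figure beside it describes a mean with a symmetric interval.

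This matters most for times bounded at zero. Eligibility includes prediabetes, and some reporting windows last only 6 hours, so it is plausible that many participants will have no time at all below 54 or above 250 mg/dL in a given window. With about 15 participants and many zeros, the usual interval for a mean can include negative times and can miss the true mean more often than its label says. At stake are the published estimates and error bars for hypoglycemia and level 2 hyperglycemia, which include safety-relevant outcomes.

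**Working it through.** **Inputs.** From the protocol: 15 completers; 95% level; variables bounded at zero; mean and SD format. Assumed, because the protocol is silent: the interval is the ordinary t interval; a share p0 of participants is exactly zero; the remaining values are exponential, or lognormal with log-SD s = 0.5 (mild skew), 1.0 or 1.5 (strong skew).

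**The plan's own figures.** The plan states no coverage figure and no expected values for these outcomes; only the 15 is used here. The recruitment target follows from it: 15/(1 − 0.40) = 25.

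**Step 1, no distribution needed.** Interval: mean ± t × SD/√n, with n = 15 and t(14 df) = 2.145. Let k of 15 values be non-zero and equal to 1, so that mean p = k/15 and SD = √[15p(1 − p)/14].

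- k = 3: p = 0.200; SD = √(15 × 0.16/14) = 0.414; half-width = 2.145 × 0.414/3.873 = 0.229; lower limit −0.029.
- k = 4: p = 0.267; SD = 0.458; half-width 0.254; lower limit +0.013.

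Equal non-zero values give the smallest SD for a given mean. So with one, two or three non-zero participants out of 15 the lower limit is negative whatever the values are. With four or more it depends on skew.

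**Step 2, coverage of the true condition mean** (nominal 95%, n = 15, 40,000 simulated samples per lognormal cell):

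| Zeros | Exponential | s = 0.5 | s = 1.0 | s = 1.5 |
|---|---|---|---|---|
| 50% | 88% | 93% | 84% | 70% |
| 70% | 83% | 90% | 79% | 64% |
| 80% | 77% | 86% | 74% | 59% |
| 90% | 63% | 75% | 63% | 49% |

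The misses are almost all on one side. In the exponential model at 80% zeros the interval lies wholly below the true mean in 23.2% of samples and wholly above it in 0.1%. If all 25 recruits contributed, the s = 1.0 column would read 86%, 83%, 79% and 70%.

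**Step 3, share of samples with a negative lower limit** (n = 15). Exponential: 53%, 76%, 90% and 79% at 60%, 70%, 80% and 90% zeros. Lognormal, s = 0.5/1.0/1.5: 6/34/65% at 50% zeros, 48/75/89% at 70%, 76/89/93% at 80%, 77/79/80% at 90%. The share stops rising at 90% because 0.9^15 = 0.206 of samples are then all zero, and their interval collapses to 0 to 0.

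**Step 4, would such variables reach the rank test?** With 50% or more zeros, Shapiro-Wilk at n = 15 rejects in 91% to 100% of samples under the lognormal models. So the mismatch between test and summary would arise in practice if the variables are that sparse.

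**Step 5, the change from control.** A t interval for the paired difference covers 96% to 100% with no effect, and 71% to 95% with an assumed 30% reduction (30% to 90% zeros, lognormal models). A negative limit is meaningful there.

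**The case against.** The strongest reply is that the trouble rests on a premise the protocol does not contain. A reader might infer that these variables are mostly zero and that the plan itself assigns them to a rank test, so that their intervals will run below zero. The documents do not support that. They give no mean, SD or share of zeros, and they name no variable for the rank route, which depends on Shapiro-Wilk. T2D is admitted with HbA1c of 6.5% or above without an upper limit, and the mix with prediabetes is not fixed, so times above 180, 181-250 or even above 250 mg/dL need not be sparse. With half the values zero and mild skew, coverage is 93% and only 6% of lower limits are negative. This stands, and the point is therefore conditional.

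Two further replies also stand. The defined effect is a change from control, for which a negative limit is valid; the objection to negative values applies only to intervals on condition means. And no CI method is named, which an article may leave to a fuller plan. Still, a t interval is the natural reading beside a mean and SD, and the time variables are themselves to be reported as percentages and hours per day, so condition summaries are in scope.

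Nor do the obvious alternatives help. A percentile bootstrap of the mean covers 81%, 79%, 73% and 62% at 50%, 70%, 80% and 90% zeros (s = 1.0), no better than the t interval. For the mean paired difference at 80% zeros it covers about 82% against 93% for the t interval (independent conditions, exponential non-zero values, 30% reduction). The Hodges-Lehmann estimate is exactly 0 in about 84% to 98% of samples at 80% to 90% zeros.

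What the reply does not remove is the text: one format is stated for all data, and it does not fit the plan's own nonnormal route.

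**Conclusion.** The point holds as a conditional reporting fault of minor weight. The universal summary rule does not match the rank route. For zero-bounded outcomes that turn out sparse, a t-based interval for a condition mean at n = 15 can include negative times and under-cover: about 88% at 50% zeros and 63% at 90% with exponential non-zero values, about 93% at 50% zeros with mild skew, and as low as 49% at 90% zeros with strong skew. These figures rest on an assumed share of zeros, an assumed shape for the rest and the t interval.

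A reader might go on to infer that the trial's tests or its power are compromised. They are not: the choice of tests does not depend on the summary format, and the sample size was set on 24-hour average glucose.

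**What to change.** Amend the summary sentence so that mean, SD and a t-based 95% CI per condition apply to variables analysed by ANOVA, and name the CI method. For any variable analysed by a rank test, report per condition the median and IQR, and the number of participants with any non-zero time with an exact binomial 95% CI. The mean may be kept as a description of total exposure, without a symmetric interval.

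The count is needed because the median alone says little: at 70% zeros the sample median is 0 in 95% of samples. The count stays informative even when nobody is affected: for 0 of 15 the exact upper limit is 1 − 0.025^(1/15) = 0.218, so the interval is 0% to 21.8%. Bootstrap and Hodges-Lehmann intervals should not be offered as the cure for mostly zero variables.

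The cost is a wording change, slightly longer tables and medians that will often be zero. No new data are needed.

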### Study Type and Design

This study will be a crossover, 3-arm, randomized controlled trial. The protocol description followed the SPIRIT (Standard Protocol Items: Recommendations for Interventional Trial) [36] and the TiDieR (Template for Intervention Description and Replication) [37] guidelines (Figure 1 and Multimedia Appendices 1-4). Upon meeting eligibility criteria and agreeing to participate, participants will undergo an anthropometrics assessment, familiarization sessions, and strength assessment before randomly carrying out 3 separate experimental sessions (2 exercise and 1 control), with each session taking place over ~48 hours, over 3 consecutive days. The order of the sessions will be randomized and they will be separated by a minimum of 4 washout days.

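### A Shapiro-Wilk test of undefined data normality chooses between ANOVA and a rank test, and can divert a valid within-person ANOVA to a weaker test

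*Protocol article*

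**What the plan says.** Study Type and Design: "This study will be a crossover, 3-arm, randomized controlled trial". Each participant therefore supplies all three conditions.

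Statistical Analysis, sample size: a repeated-measures ANOVA in G*Power with "effect size of 0.2 (for 24-hour average glucose concentrations"), "power (probability of error type 1 β) of 0.95" and "correlation among repeated measurements of 0.7", giving 15 participants.

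Statistical Analysis, test selection: "For the analysis of data normality, we will perform the Shapiro-Wilk test. For normally distributed data, ANOVA will be used with 1 source of variation", that source being experimental condition, with Tukey comparisons after a significant result. Then: "For nonnormal data, the Kruskal-Wallis test or Friedman test will be used as appropriate".

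The text does not define which values are tested for normality. It does not mention residuals or within-person differences in that role, and it does not say whether conditions are tested separately or together. No single analysis is fixed for 24-hour average glucose, the variable on which the trial is sized.

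**The concern.** A raw glucose value is a participant's own level plus a within-person error. The participant's level is the same under all three conditions and drops out of every contrast between them, so the repeated-measures ANOVA needs approximate normality only of the within-person part. A Shapiro-Wilk test on raw values responds to both parts, and at the stated correlation the larger part is the one that cancels. Skew between participants can then trigger the rank test although the ANOVA assumption holds.

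Such skew is plausible. The trial enrols prediabetes together with "T2D (fasting glycemia 126 mg/dL or above or HbA_1c_ 6.5% or above), diagnosed by a medical doctor", and no upper glucose or HbA1c limit is given.

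What is at stake is power and consistency. Friedman uses only the order of the three values within a person. Kruskal-Wallis, also allowed, ignores that the values come from the same person. The Introduction's hypothesis is that effort will not affect glycemic control, so lost power leans toward the expected answer. With 14 CGM variables over several time windows, closely related outcomes could also be judged by different tests.

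**Working it through.** **Inputs from the protocol.** N = 15; three conditions; correlation ρ = 0.7; effect size 0.2, read as Cohen's f because that is what G*Power uses for ANOVA; α = 5%; nonsphericity correction ε = 0.5; power 0.95 (achieved 0.96); 25 recruited.

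**The plan's own figure.** The G*Power interaction formula has noncentrality λ = N·m·f²·ε/(1−ρ), with m measurements and k groups. The article states neither k nor m. Assuming k = 3 and m = 48:
- λ = 15 × 48 × 0.04 × 0.5 / 0.3 = 48
- df1 = 2 × 47 × 0.5 = 47; df2 = 12 × 47 × 0.5 = 282
- power 0.956, matching the stated 0.96
- recruitment: 15 / (1 − 0.40) = 25

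For the three-condition comparison in the analysis text (m = 3, no ε correction), λ = 15 × 3 × 0.04 / 0.3 = 6 on 2 and 28 df, and power is 0.54. That gap is a separate matter. It is used here only as the starting power at f = 0.2.

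**Share of raw variance that cancels.** Between-participant share = ρ = 0.7; within-person share = 1 − 0.7 = 0.3.

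**Simulation model.** y = √0.7 · (participant effect) + √0.3 · (normal error) − d · (exercise), with the participant effect scaled to unit variance. The errors are exactly normal, so the repeated-measures ANOVA is valid throughout. The shape of the participant effect is assumed, because the article does not give it. The switching rule (any of three conditions rejecting at 5%) is also assumed.

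| Participant effects | At least one raw condition rejects |
|---|---|
| Normal | about 14% |
| 50/50 two-group mix, 4 SD apart | about 13% |
| 75/25 mix, 2 / 3 / 5 SD apart | about 14% / 19% / 33% |
| Gamma, shape 4 | about 24% |
| Lognormal, σ = 0.5 | about 34% |
| Exponential | about 42% |

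Reference rates in the same simulations:
- any of the three within-person differences: about 14% (13-15% across shapes)
- one test on the model residuals: about 3%
- one raw condition alone: 5-21%

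**Power.** With d = 0.57 SD, f² = 0.57² × 2/9 = 0.0722 and λ = 15 × 3 × 0.0722 / 0.3 = 10.8, which gives ANOVA about 80%. At that effect Friedman has about 65% and Kruskal-Wallis 17-29%.

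**Average loss, Friedman as fallback.** This is roughly the diverted share × (80 − 65):
- 0.05 × 15 = 0.8 points (single-condition check, normal participants)
- 0.14 × 15 = 2.1
- 0.24 × 15 = 3.6
- 0.42 × 15 = 6.3

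The range is about 1-6 points.

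**Average loss, Kruskal-Wallis as fallback.** With normal participant means, 0.14 × (80 − 17) = 8.8 points, about 8 when simulated directly. With skewed or unbalanced participant means, the whole rule has 57-66% power, a loss of 80 − 66 = 14 to 80 − 57 = 23 points.

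**At the protocol's f = 0.2.** ANOVA 0.53-0.55 and Friedman 0.39-0.41. With skewed participants, the two-stage rule has 0.48-0.49 with Friedman and 0.35-0.38 with Kruskal-Wallis.

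**Type I error.** Near 5% with Friedman as fallback; below nominal (about 3%) with Kruskal-Wallis.

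**The case against.** The strongest reply is that the article leaves the tested values undefined. Shortly before the normality sentence it expresses the effect as change from control; if those changes are what is tested, most of the problem disappears. This cannot be excluded. But that sentence describes how the effect is calculated, while the ANOVA factor is experimental condition, so raw values per condition are the plainer reading. The wording at least permits the wrong check.

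Several stronger claims that a reader might infer do not stand:
- **That one failing condition out of three switches the test.** The article states no such rule. The any-condition figures rest on an assumption, and a single-condition check rejects in only 5-21%.
- **That wrongful diversion runs at several times the nominal 5%.** That sets an any-of-three rate against a single test. The like-for-like reference is about 14%, so normal participant means show no excess.
- **That mixing prediabetes with T2D is enough to trigger the switch.** A balanced two-group mix gives about 13%, no excess. Material excess needs right skew or a wide, unbalanced gap, and the absence of a ceiling does not establish either.
- **That the pre-test ignores the within-person errors.** Raw values contain them, at 30% of the variance.

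It is also fair that a rank method is reasonable for bounded, zero-heavy variables such as time below range. The lack of a named post hoc test on the rank branch may be settled in an analysis plan that is not shown, and is not counted here.

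**Conclusion.** The point holds in a limited form. The article states a decision rule, and on its plain reading that rule checks values whose distribution the crossover comparison does not need to be normal. It can therefore send a valid within-person ANOVA to a weaker test.

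The excess over the like-for-like 14% appears when participant means are right-skewed (24-42%) or form a widely separated, unbalanced mix. It is absent when they are normal or evenly split. The average cost is modest with Friedman (about 1-6 points) and substantial only if Kruskal-Wallis is used (about 8-23 points). Nothing here supports a claim of excess false positives.

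These sizes assume N = 15, ρ = 0.7, normal within-person errors, and the participant shapes and switching rules listed above. They also read the ANOVA as a within-person one, in line with the design and the sample-size method. The point is strongest for average glucose and similar continuous variables.

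**What to change.** Replace the normality-test switch with an analysis fixed in advance:

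1. Analyse 24-hour average glucose and the other roughly continuous CGM variables (area under the curve, SD, coefficient of variation) with a repeated-measures or mixed model that includes participant, whatever the raw distribution.
2. Check that model's residuals with a Q-Q plot. Do not let a Shapiro-Wilk test of raw data choose the method.
3. Report Friedman as a stated sensitivity analysis.
4. Remove Kruskal-Wallis from the within-person comparisons.
5. Assign the zero-heavy variables (time below range, level 2 hypoglycemia and hyperglycemia) in advance to Friedman, with paired Wilcoxon signed-rank contrasts.

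This costs a few sentences of analysis text and needs no new data or participants. The downside is slightly less robustness if the within-person differences are heavy-tailed, which the rank sensitivity analysis covers.
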